# Study protocol for a randomized controlled trial on the effect of the Diabetic Foot Guidance System (SOPeD) for the prevention and treatment of foot musculoskeletal dysfunctions in people with diabetic neuropathy: the FOotCAre (FOCA) trial I

**DOI:** 10.1186/s13063-019-4017-9

**Published:** 2020-01-13

**Keywords:** Diabetic foot, Preventive care, Foot-related exercises, Self-management, eHealth, Musculoskeletal function, Rehabilitation technology

## Abstract

**Background:**

This study is part of a series of two clinical trials. Taking into account the various musculoskeletal alterations of the foot and ankle in people with diabetic peripheral neuropathy (DPN) and the need for self-care to avoid more serious dysfunctions and complications, a self-manageable exercise protocol that focuses on strengthening the foot muscles is presented as a potentially effective preventive method for foot and gait complications. The aim of this trial is to investigate the effect of a customized rehabilitation technology, the Diabetic Foot Guidance System (SOPeD), on DPN status, functional outcomes and gait biomechanics in people with DPN.

**Methods/design:**

Footcare (FOCA) trial I is a randomized, controlled and parallel two-arm trial with blind assessment. A total of 62 patients with DPN will be allocated into either a control group (recommended foot care by international consensus with no foot exercises) or an intervention group (who will perform exercises through SOPeD at home three times a week for 12 weeks). The exercise program will be customized throughout its course by a perceived effort scale reported by the participant after completion of each exercise. The participants will be assessed at three different times (baseline, completion at 12 weeks, and follow-up at 24 weeks) for all outcomes. The primary outcomes will be DPN symptoms and severity classification. The secondary outcomes will be foot–ankle kinematics and kinetic and plantar pressure distribution during gait, tactile and vibration sensitivities, foot health and functionality, foot strength, and functional balance.

**Discussion:**

As there is no evidence about the efficacy of rehabilitation technology in reducing DPN symptoms and severity or improving biomechanical, clinical, and functional outcomes for people with DPN, this research can contribute substantially to clarifying the therapeutic merits of software interventions. We hope that the use of our application for people with DPN complications will reduce or attenuate the deficits caused by DPN. This rehabilitation technology is freely available, and we intend to introduce it into the public health system in Brazil after demonstrating its effectiveness.

**Trial registration:**

ClinicalTrials.gov, NCT04011267. Registered on 8 July 2019.

## Background

Diabetic peripheral neuropathy (DPN) is one of the most prevalent chronic complications of diabetes mellitus (DM) [1]. It is estimated that between 12 and 50% of people with DM have some degree of DPN [2]. As a result of the sensorimotor impairments caused by DPN, several musculoskeletal dysfunctions are present. These include alterations in the joints surrounding tissues, reducing their range of motion [3–5], and reduction in functionality and strength due to deterioration of the intrinsic foot and lower leg muscles [6–8].

People with DM commonly present with alterations in gait biomechanics, such as reduced gait speed, decreased ankle dorsi and plantarflexion [5, 9], delayed muscle activations in the leg and thigh [5, 10–15], reduced ankle and increased hip joint moments [16–18], and altered plantar pressure distribution patterns that increase the risk of developing plantar ulcers [19–23]. Due to these changes, individuals with DM may have difficulties performing their daily locomotor activities, which compromises their functionality and negatively impacts their quality of life [24–26].

Recent studies have evaluated the effects of performing specific exercises for musculoskeletal deficits in people with DPN on clinical and biomechanical variables and have concluded that they can reduce peak plantar pressure during gait [27–33], minimize DPN symptoms and loss of sensitivity [30, 33], increase the mobility of the foot–ankle complex and the first metatarsophalangeal joint [27, 32–34], and maximize the strength of the foot–ankle muscles [30, 34, 35]. However, for some of the above-cited interventions successful results were not maintained at follow-up [36], which suggests that self-care after any intervention is pivotal for the maintenance of the health benefits achieved when managing DM and its chronic complications. To accomplish this goal, an intervention program should include various care modalities—such as education, self-assessment, foot self-management, foot self-care, medication, and proper nutrition—in addition to the most current approaches, as exercise can help to prevent musculoskeletal complications due to disease progression [37].

Education through software or booklets that provide guidelines for self-care and at-home exercises can be potentially successful alternatives to traditional treatments [38–40]. The accessibility of and advances in modern technology have made it possible to use electronic devices to improve adherence to health prevention and treatment, especially for chronic diseases [41].

Ferreira et al. [40] have developed and validated free, publicly available software, the Diabetic Foot Guidance System (SOPeD) (www.soped.com.br), with general guidelines on foot self-care and self-assessment and a personalized protocol including balance, strengthening, and stretching exercises for the treatment and prevention of the most common foot–ankle musculoskeletal deficits due to DM and DPN. This software is designed to provide and monitor exercises, facilitate self-care, and improve autonomous performance of daily living tasks [40]. However, its efficacy for the treatment of people with DM and DPN has not yet been proven and, to date, no studies have been performed to evaluate the effects of a rehabilitation technology capable of personalizing specific therapeutic foot exercises aimed at prevention and treatment of musculoskeletal deficits and complications in people with DPN.

The primary aim of this superiority randomized controlled, singe-blind, two-parallel-arm trial, the Footcare (FOCA) trial I, is to investigate the effects of the customized foot-related exercise software SOPeD on DPN symptoms and severity after 12 weeks (intervention completion) and 24 weeks (follow-up) in patients with DPN. The secondary aims are to investigate the effects of this intervention at 12 and 24 weeks on foot–ankle biomechanics and plantar pressure during gait, tactile and vibration sensitivities, foot health and functionality, foot strength, and functional balance.

We hypothesize that the therapeutic customized exercise protocol will reduce DPN symptoms and severity as well as improve foot health and functionality status, plantar sensitivity (tactile and vibration perceptions), and functional balance scores. We also hypothesize that the protocol will produce beneficial biomechanical changes during gait that denote an improvement in foot–ankle kinematics and in the plantar pressure distribution. Such changes may include: 1) an increase in the ankle range of motion in the sagittal plane; 2) an increase in the ankle extensor moment and power; 3) an increase in the ankle flexor moment and eccentric power during the heel-strike phase; 4) a reduction in peak pressure over risky areas; and 5) improved foot rollover by redistributing plantar pressure during gait.

It is important to highlight that intervention programs in this population rarely include any foot-related exercises focusing on the most common and frequently described musculoskeletal foot–ankle deficits. The present proposal uses a new paradigm that focuses on autonomous and independent use of a rehabilitation technology to improve self-care and management, with the aim of enhancing compliance to preventive strategies in people with DM.

## Methods and design

### Trial design

This study is part of a series of two clinical trials: the FOCA trial I (SOPeD intervention) and FOCA trial II (booklet intervention). The FOCA trial I is a superiority, single-blind, randomized controlled trial with two parallel arms where participants will be randomized into one of two groups: the intervention group that will perform foot-related exercises included in the SOPeD; and the control group that will not receive any specific intervention besides the treatment recommended by a health care professional. This trial will have an allocation ratio of 1:1.

People with DM and DPN will be recruited from the Department of Endocrinology of the Hospital das Clínicas of the School of Medicine of the University of São Paulo, Brazil, and will be referred to a physical therapist who will perform the group allocation. The participants will then be referred to another physical therapist who will perform the initial blind assessment. All participants allocated to the intervention group will participate in a protocol of monitored and customized therapeutic exercises for the foot–ankle complex using the SOPeD software three times a week for 12 weeks [40]. After the 12-week period, the intervention group participants will be encouraged to continue exercising until the end of the study following the same schedule set during the intervention period. The participants allocated to the control group will not receive any specific intervention besides the regular treatment recommended by health care professionals (doctors, nurses, and podiatrists). If proven effective, the benefits of the foot-related exercise protocol will be explained and offered to all control participants at the end of the study.

All participants will be assessed at baseline, 12 weeks (end of intervention) and 24 weeks (follow-up). Assessments will record DPN symptoms and severity (primary outcomes) and all other secondary outcomes.

The Consolidated Standards of Reporting Trials (CONSORT) 2010 guidelines will be followed. The study was approved by a research ethics committee (CAAE: 90331718.4.0000.0065) and was registered at ClinicalTrials.gov on 8 July 2019 (study identifier NCT04011267).

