### Participants and recruitment

This study is currently recruiting patients (study start date 1 August 2019) with a medical diagnosis of DM and DPN from the Department of Endocrinology of the Hospital das Clínicas of the School of Medicine of the University of São Paulo through telephone contact. Sixty-two patients with DPN will be recruited. The potential participants will be interviewed by telephone and, upon selection, assessed in the laboratory to confirm all eligibility criteria. This first laboratory assessment will represent the baseline condition (blind assessment).

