### Randomization, allocation, and blinding

pt?>The randomization schedule has been prepared using Clinstat software [44] by an independent researcher (Researcher 1) who is not aware of the numeric coding for the control group and intervention group. A numeric block randomization sequence is kept in opaque envelopes.

Potential participants will be assessed through an initial screening that consists of checking the eligibility criteria, classifying the DPN severity, and identifying those with a lower probability of adherence to the intervention due to depression. After the initial screening, participants who meet the inclusion criteria will be randomized to either the intervention group or control group. After the agreement to participate and assignment in the research, the allocation of the groups will be made by another independent researcher (Researcher 2) who is also unaware of the codes. All participant personal data will be kept confidential before, during, and after the study by encoding the participants’ names. Only the physiotherapist (Researcher 3), who is the main researcher responsible for the intervention, is aware of who is receiving the intervention. Researcher 3 is also responsible for the remote monitoring of the intervention by the SOPeD software and by telephone. One physiotherapist and an occupational therapist (Researchers 4 and 5), who are also blind to the treatment allocation, will be responsible for all clinical, functional and biomechanical assessments. Researchers 3, 4, and 5 are blind to the block size used in the randomization procedure. The trial statistician will also be blind to treatment allocation until the main treatment analysis has been completed. The trial design is open label where only the outcome assessors are blinded so unblinding will not occur.

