#### DPN symptoms

DPN symptoms will be assessed by the Brazilian version of the Michigan Neuropathy Screening Instrument [48]. This self-administered questionnaire is comprised of 15 questions about symptoms and events related to foot sensitivity. The answers are summed to get a total score ranging from 0 to 13 (with 13 representing the worst DPN).

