## Trial status

ClinicalTrials.gov identifier NCT04011267, version 1.0, July 8 2019. Registered on 8 July 2019 and last updated on 9 September 2019. Participant recruitment began on 1 August 2019 and is expected to continue until the middle of 2021. Randomization of the participants was performed on the same day.

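### The protocol article contradicts itself on whether allocation precedes the baseline assessment; the Trial design order could expose a self-reported primary baseline and the entry check to known allocation

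*Protocol article*

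**What the plan says.** Three sections of the protocol article describe the sequence of events.

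- **Trial design:** recruited patients first see a therapist whose task is to "perform the group allocation. The participants will then be referred to another physical therapist who will perform the initial blind assessment".
- **Participants and recruitment:** after a telephone interview, patients are "assessed in the laboratory to confirm all eligibility criteria". The next sentence identifies that visit with baseline: "This first laboratory assessment will represent the baseline condition (blind assessment".
- **Randomization, allocation, and blinding:** the screening consists of "checking the eligibility criteria, classifying the DPN severity, and identifying those with a lower probability of adherence to the intervention due to depression". It continues: "After the initial screening, participants who meet the inclusion criteria will be randomized to either the intervention group or control group".

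Two other places touch on timing. Participant timeline calls T0 a preintervention baseline without placing it before or after randomisation. Trial status, after giving the recruitment start date, says "Randomization of the participants was performed on the same day".

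The exposed measures are described as follows. DPN symptoms, a primary outcome, come from the Michigan Neuropathy Screening Instrument: "This self-administered questionnaire is comprised of 15 questions about symptoms and events related to foot sensitivity". The second primary outcome, the fuzzy severity score, takes one of its three domains from that instrument. A fuzzy score of at least 2 is also an entry criterion (Inclusion criteria; Screening measures). The randomisation section calls the trial open label, with only outcome assessors blinded.

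**The concern.** Baseline is one half of the T0 to T12 change, and the planned analysis tests the treatment-time interaction. If participants answer the T0 questionnaire knowing their arm, a difference between arms can arise at T0 that the treatment did not cause, and it passes into the interaction. Blinded assessors do not protect a questionnaire that patients complete themselves.

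Eligibility has a similar problem. If the laboratory visit that decides whether the fuzzy score reaches 2 takes place after allocation, people found ineligible have to be removed after randomisation. Such removals can differ between arms and erode the intention-to-treat comparison that the article promises. Recruitment is described as under way, so some patients may already have been handled in one order or the other.

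**Working it through.** **1. The two orders side by side.**

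- Trial design: recruitment, group allocation, then the initial blind assessment.
- Participants and recruitment: telephone selection, then a laboratory visit that both confirms eligibility and is the baseline.
- Randomization, allocation, and blinding: screening (eligibility and severity classification), then randomisation of those who qualify.

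The second and third combine into eligibility and baseline first, randomisation second. The link is inferential: the randomisation section speaks of an initial screening and does not call it baseline, but the recruitment section makes the laboratory eligibility visit the baseline. The first order is the reverse. The preintervention label does not settle it, because a visit after allocation but before the first exercise session is still preintervention. The same-day sentence does not settle it either.

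**2. What would be exposed under the Trial design order.** The whole symptom score, one of the three inputs to the fuzzy score, and the entry threshold of 2. The other two fuzzy inputs, monofilament and tuning fork, are tests given by blinded assessors.

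**3. Reproducing the plan's sample size, to get a scale for the effect.** Inputs from Sample size and statistical analyses: effect size 0.20, two groups (k = 2), two repeated measures (m = 2), alpha 0.05, power 0.80. The article gives no correlation between measures, so ρ = 0.5 is assumed. Treating 0.20 as Cohen's f:

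- λ = N·f²·m/(1 − ρ) = 52 × 0.04 × 2/0.5 = 8.32, with 1 and 50 degrees of freedom.
- Power is 0.807 at N = 52 and 0.791 at N = 50, so the stated 52 reproduces.

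**4. What f = 0.20 means as a difference in change.** In a 2 × 2 interaction the cell effects are ±0.2 SD, so the between-arm difference in change is 4 × 0.2 = 0.8 SD. Check with 26 per arm: SD of change = √(2(1 − 0.5)) = 1, and λ = (26/2) × 0.8² = 8.32, the same value.

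**5. Illustration of a contaminated baseline.** Assume no true effect and a shift of b SD at T0 in one arm only, gone by T12. The article gives no figure for b. The change-score contrast absorbs all of b. Its standard error is 1 × √(2/26) = 0.277. For b = 0.2:

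- 0.2/0.277 = 0.721.
- Two-sided rejection rate = Φ(−1.960 + 0.721) + Φ(−1.960 − 0.721) = 0.108 + 0.004 ≈ 0.111.

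Range at ρ = 0.5: 6.5% for b = 0.1, 11.1% for 0.2, 19.1% for 0.3, 43.8% for 0.5. For b = 0.2 the rate is about 9% at ρ = 0.3 and 15% at ρ = 0.7. Relative to the planned effect, 0.2/0.8 = one quarter. If baseline were instead a covariate with slope 0.5, then 0.5 × 0.2 = 0.1 SD would remain.

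**The case against.** The best defence is that the section governing randomisation, read with the recruitment section, already gives the sound order, and that the outlier is one summary sentence under Trial design. The CONSORT flow chart (Fig. 1) and the SPIRIT schedule (Table 1) are not reproduced in the text at hand and may show the intended order. This makes a drafting slip plausible. It does not remove the contradiction in the text.

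A reader might infer that participants know their arm when they answer the T0 questionnaire. The article does not say so. It describes an allocating researcher who is unaware of the codes and a single physiotherapist who knows who receives the intervention. Even if allocation came first, a patient could carry a coded assignment through T0 and learn the arm later. The open-label statement gives no time of disclosure. This part of the objection stands, and the bias is therefore only a possibility.

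A reader might also set the assumed 0.2 SD shift equal to the 0.20 in the sample-size section. That is wrong on two counts. The 0.20 behaves as Cohen's f, which corresponds to 0.8 SD in change. It was also taken from forefoot peak pressure, an instrumented secondary outcome; for DPN symptoms the article cites 0.52.

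Finally, awareness of the arm may colour self-report at T12 as well. A shift of the same size and direction at both visits would cancel in the change. The illustration needs a shift that does not persist, and nothing in the article fixes its direction or size.

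**Conclusion.** The contradiction is real and sits in the current text: one section allocates before baseline, while two others together place baseline before randomisation. The harm is conditional. It requires that the Trial design order is the one used and, for the self-reported scores, that participants learn their arm before T0. Post-randomisation exclusions require only the first condition.

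Under the stated assumptions (0.2 SD shift in one arm, absent at T12, 52 patients, ρ = 0.5), the two-sided false-positive rate rises from 5% to about 11%, and the shift is about a quarter of the planned difference in change. This illustrates sensitivity and does not estimate bias in this trial. The article does not support the claim that the baseline is in fact biased. Nor does the Trial status sentence establish a single randomisation day for everyone; it is ambiguous and carries little weight.

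**What to change.** Rewrite the Trial design sentence to match the recruitment and randomisation sections: laboratory eligibility check and the full T0 battery, including the questionnaire, and only then allocation. Check that the flow chart and schedule show the same order. Reword the Trial status sentence so that it is clear what happened on the same day as what.

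For patients already enrolled, record whether T0 was completed before allocation. If it was not for any of them, repeat the primary analysis without those patients as a sensitivity analysis.

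The cost is protocol wording, a fixed visit order and one recorded item per patient, with no extra visits, staff or participants. It should be done while recruitment is under way, because a baseline taken after allocation cannot be recovered later.

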### Study setting

The assessments will be performed at the Laboratory of Biomechanics of Human Movement and Posture at the Physical Therapy, Speech and Occupational Therapy Department of the School of Medicine of the University of São Paulo, São Paulo, Brazil. The participants allocated to the intervention group will perform the exercises by themselves in their homes, but the first session will be in an ambulatory setting to provide them with a reliable therapeutic environment and treatment assistance. This first session will be conducted by a physical therapist who will teach and supervise the correct execution of the exercises performed while using the software.

### Participants and recruitment

This study is currently recruiting patients (study start date 1 August 2019) with a medical diagnosis of DM and DPN from the Department of Endocrinology of the Hospital das Clínicas of the School of Medicine of the University of São Paulo through telephone contact. Sixty-two patients with DPN will be recruited. The potential participants will be interviewed by telephone and, upon selection, assessed in the laboratory to confirm all eligibility criteria. This first laboratory assessment will represent the baseline condition (blind assessment).

### Eligibility criteria

#### Inclusion criteria

Adults (age 18–65 years) with DM type 1 or 2 and mild, moderate, or severe DPN confirmed using fuzzy software (www.usp.br/labimph/fuzzy; score ≥2) who have the ability to walk independently in the laboratory and have access to an electronic device (computer, mobile device, tablet, etc.) and the SOPeD exercise software will be included in the study.

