### Trials arms

#### Control group

Participants in the control group will not receive any specific intervention besides the treatment recommended by the health care team (doctors, nurses, and podiatrists), which will include pharmacological treatment as well as self-care and foot care recommendations as per international consensus. If proven effective, the benefits of the foot-related exercises protocol will be explained and offered to all control group participants at the end of the study.

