#### Intervention group

Patients in the intervention group will perform customized foot-related exercises included in the SOPeD software three times per week at home for a 12-week period. These will be remotely supervised by Researcher 3 after the first in-person supervised session at the department. They will receive access and all instructions on how to use the tool on the first day. During the follow-up period, intervention group participants will be encouraged to follow the same schedule set by the project till the end of the study (24 weeks after allocation), but will not be remotely monitored, and will be encouraged to continue exercising in the future.

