### Outcomes and measures

#### Participant timeline

Participants in the intervention group and control group will be assessed at the preintervention baseline (T0), at the end of the 12-week intervention (T12), and at follow-up 24 weeks after baseline (T24). A physiotherapist and an occupational therapist (Researchers 4 and 5) who are blinded to group allocation will perform all the assessments. All participants will maintain contact with Researcher 3 throughout the follow-up period through the web software, email, and telephone. Table 1 shows the schedule of enrollment, interventions, and assessment according to the SPIRIT guidelines [42].

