#### Foot health and functionality

The Brazilian version of the Foot-Health Status Questionnaire (FHSQ-BR) [51] will be used to determine foot health. This instrument is divided into three domains, and this study will use domains I and II. Domain I evaluates the foot in four dimensions: pain, function, footwear, and general health. Domain II evaluates the general state of health in four dimensions: general health, physical activity, social capacity, and vitality. Domains I and II are comprised of questions with answers in affirmative sentences and a Likert-type scale. Domain III is comprised of the collection of participants’ general demographic data. Domains I and II receives a score from 0 to 100, where 100 expresses the best condition and 0 the worst. The data will be analyzed using the FHSQ version 1.03 software (Care Quest—Researching Healthcare Solutions, Australia).

In addition to the face-to-face assessment, every 30 days the participants will self-assess their DPN symptoms as well as the health status of their feet by completing both the FHSQ-BR questionnaire and undergoing a physical examination of the foot using the SOPeD software (www.soped.com.br), in which the participant can drag markers that represent major foot changes (calluses, cracks, fissures, mycoses, toe deformities, ulcers, and amputations) onto images of both feet (Fig. 2). At the end of these monthly evaluations, the participant and the main researcher will be provided with a report related to the patient’s conditions and whether or not they are still able to perform the exercise protocol.

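### As written, both arms have access to and use SOPeD, which contains the exercises under test, and control use of those exercises is neither clearly ruled out nor recorded

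*Protocol article*

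**What the plan says.** Three sections, read as written, put participants of both arms into SOPeD:

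- **Inclusion criteria:** eligible adults are those who "have access to an electronic device (computer, mobile device, tablet, etc.) and the SOPeD exercise software will be included in the study". Under Randomization, allocation, and blinding, people are randomised only after they have met these criteria.
- **Participant timeline**, which opens by naming both groups: "All participants will maintain contact with Researcher 3 throughout the follow-up period through the web software, email, and telephone".
- **Foot health and functionality:** "every 30 days the participants will self-assess their DPN symptoms as well as the health status of their feet", by means of a questionnaire and a foot examination done in SOPeD.

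The Background describes SOPeD as free and open to the public. It is a single tool, "with general guidelines on foot self-care and self-assessment and a personalized protocol including balance, strengthening, and stretching exercises".

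Two sections point the other way. Control group: "Participants in the control group will not receive any specific intervention besides the treatment recommended by the health care team". Intervention group, speaking of that arm alone: "They will receive access and all instructions on how to use the tool on the first day".

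The limits on crossover are in three places. The Exclusion criteria rule out physiotherapy during the intervention period. The Intervention section advises both arms against starting new foot-ankle physiotherapy, asks anyone who does so to report it, and then excludes them. The same section restricts the SOPeD forum to people of the same group.

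**The concern.** The trial compares exercise delivered by software with no exercise, so it depends on controls not doing the exercises. If controls must have the software to enter, and then use it for contact and monthly self-assessment, they are repeatedly brought to the place where the exercises are. Any control who exercises shrinks the difference between arms, and an analyst could not see from the stated data that this had happened.

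If the monthly self-assessment is meant for the intervention arm only, a different problem arises. That arm alone would repeatedly rate its own neuropathy symptoms and receive a report. One primary outcome is a self-administered symptom questionnaire, its content feeds the other (the fuzzy severity score), and participants know their allocation.

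**Working it through.** **1. Who has access.** The entry criterion precedes allocation, so it applies to everyone. The Intervention group section treats access as something that arm receives on its first day. Access cannot be both a condition of entry for all and part of what one arm is given, unless the criterion means only that a person would be able to use the site. The article does not say so.

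**2. Who uses it.** The contact sentence says all participants, in a section that has just named both groups. The self-assessment sentence names no arm and stands in the outcomes part, which covers both. Its last clause, on "whether or not they are still able to perform the exercise protocol", fits only people who are exercising. The text therefore supports either reading.

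**3. What the safeguards would catch.** The advice concerns new physiotherapy programs, and the article does not say that unsupervised use of SOPeD exercises counts as one. Detection depends on the participant volunteering it, and disclosure leads to exclusion. Follow-up of missed logins is stated for the intervention group only. Excluding controls after randomisation because they exercised also conflicts with the intention-to-treat analysis in Sample size and statistical analyses.

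**4. Illustration of dilution.** From that same section: f = 0.20, two groups (k = 2), two repeated measures (m = 2), alpha 0.05, power 0.80, N = 52, raised to 62 for dropout. The correlation between measures is not stated; rho = 0.5 is assumed.

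For the within-between interaction, lambda = N × f² × m / (1 − rho), with df1 = (k − 1)(m − 1) = 1 and df2 = (N − k)(m − 1) = 50.

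The plan's figure first: lambda = 52 × 0.04 × 2 / 0.5 = 8.32, power 80.7%. At N = 50 power is 79.1%, so 52 is reproduced. With rho = 0.3 the required N would be 72 and with rho = 0.7 it would be 32, so 0.5 is the value that fits among those tried.

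Let c be the share of controls who gain the full exercise effect, with the spread within groups unchanged. Then f becomes 0.20 × (1 − c):

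| c (assumed) | f | lambda at 52 | power, 52 evaluable | power, 62 evaluable | evaluable N for 80% |
|---|---|---|---|---|---|
| 0 | 0.20 | 8.32 | 80.7% | 87.3% | 52 |
| 10% | 0.18 | 6.74 | 72.1% | 79.6% | 64 |
| 20% | 0.16 | 5.32 | 61.9% | 69.8% | 80 |
| 30% | 0.14 | 4.08 | 50.8% | 58.3% | 104 |

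**The case against.** A reader might infer that the protocol hands controls the intervention itself, with nothing to prevent or detect it. The documents do not support that. No section assigns exercises to controls. Both arms get advice, a duty to report and an exclusion rule, and the forum is split by group. Messaging and self-assessment are not the exercise pages. The tested package also includes a supervised first session, remote monitoring and reminders, which a control who opens a public website does not receive. Controls already get foot-care advice as usual care, so reading such guidance in SOPeD is hardly contamination.

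The entry criterion can be taken as a feasibility screen. Because the site is public, deleting the phrase would not by itself remove anyone's access. The article also uses *all participants* loosely: the Intervention section puts to all of them a question about enjoying the exercises. Table 1 and Figure 1 were not visible in the text reviewed and may show which arm does the monthly self-assessment.

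On size, no contamination rate is given, and full benefit in every contaminated control is a worst case. The 0.20 belongs to forefoot peak pressure, a secondary outcome. The larger 0.52 given for symptoms is on an unstated scale; if it were also an f, power at 52 would remain above 99% even at c = 30%.

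On the one-arm reading, the monthly assessment names the foot-health questionnaire and a foot examination, not the Michigan instrument, so neither the direction nor the size of a bias is established.

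All this narrows the point without removing it. The sections still conflict, the safeguards do not mention the most obvious route of crossover, and no record of control exercise use is described.

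**Conclusion.** The point holds in a limited form. The article does not separate control access to SOPeD from access to its exercise program, and its sections disagree on who has and uses the software. The existing safeguards are general, rest on self-report, and act through an exclusion that works against intention to treat. If the monthly self-assessment is for one arm only, the arms differ in repeated symptom self-rating before an open-label, self-reported primary outcome.

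The direction of contamination is clear: towards no effect. Its amount is not known. The fall from about 81% to 72%, 62% and 51% depends on the assumed 10%, 20% and 30% of controls gaining the full effect, on rho = 0.5, and on the f = 0.20 used for sizing. It shows that a plan with little spare power is sensitive to modest crossover. It does not forecast what will happen, and it gives no figure for the symptom outcome. The point is worth acting on because the remedy is cheap.

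**What to change.** Reconcile Inclusion criteria, Control group, Intervention group, Participant timeline, Foot health and functionality, and the crossover advice in Intervention, checking them against Table 1. Specifically:

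- At entry, require a device and internet access instead of access to SOPeD.
- Limit control contact to email and telephone, or give controls an account without the exercise pages until T24.
- Collect the monthly self-assessment identically in both arms, or drop it.
- State whether the advice to both arms covers SOPeD exercises.
- At T12 and T24, ask about use of SOPeD and foot exercises, check registration or login records for controls, and report the result by arm.
- Keep participants who report such use in the intention-to-treat analysis.

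The cost is a short amendment, an account setting and one question at visits already planned. The remaining weakness is that a public site can be measured but not fully blocked.
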